### Outcomes

#### Primary outcome measures

i.Conceptual and behavioural change from utilising the historical FRAT.ii.Change in knowledge of evidence-based practice for falls screening and prevention in hospitalsiii.Provide clinical leaders in cohort 2 with the skills to enable them to deliver an effective education program to other clinicians.

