Research into the impact of education interventions on falls within hospitals has mainly focussed on patient education [14] and many interventions fail to adequately describe the educational methods employed [15]. As a precursor to this study, a scoping review was performed to determine the extent of the research evidence and design elements, for education interventions for health professionals in falls screening and prevention. There were few studies on this topic. One study described the outcomes of a half day education programme about fall and fracture prevention for staff given by specialist osteoporosis nurses in care facilities [16]. It did not find evidence for a reduction in the rate of falls [16] and the quality of evidence was assessed in a recent Cochrane review as being very low [17]. A pilot cluster-randomised trial in residential aged care evaluated an educational programme to improve staff connections, communication, and problem solving for the implementation of a falls quality improvement programme [18]. This trial of 546 eligible clinicians in four intervention nursing homes, did not find a change in falls rates. Notably, few education studies discussed in depth the educational approaches used, or whether theoretical principles were incorporated into their design [19].

The aims of the current study are to: (i) Investigate the self-reported views of hospital clinicians of their knowledge, clinical practice, confidence, motivation and attitudes towards screening for falls risk using traditional and contemporary approaches; (ii) Examine perceptions of an education intervention designed to communicate the latest evidence on falls screening and how to implement a new evidence-based Falls Screening Tool into daily clinical practice; (iii) Determine the effectiveness of the educational program content and delivery in supporting behaviour change for falls screening in hospitals. We shall also explore the views and experiences of health professionals on hospital falls risk screening and historical FRATs more generally.

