## Methods/ design

### Design

This study is part of a large National Health and Medical Research Council of Australia partnership grant program of work, on falls prevention in hospitals ([name] et al., GNT1152853). For the larger trial, ten Australian hospitals will be randomised to an intervention group (five hospitals using a new Falls Screening Tool), or a control group (five hospitals continuing to use the historical FRAT form) by another organisation (The University of Melbourne). The new Falls Screening Tool removes the risk assessment component from the historical FRAT form and associated summary scores, yet maintains other components for falls mitigation. This education trial will be conducted at the 5 intervention hospitals.

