### Data collection

A Pre and Post-test design will be used, elaborated through a mixed methods research approach, with the qualitative data helping to build on the initial quantitative results [21]. Data will be collected via de-identified surveys (using the participants’ initials and last three digits of their mobile telephone number) and individual telephone interviews. Multiple time points will be used for data collection from surveys:

(1) Pre-test: Immediately prior to the education program.

(2) Post-test 1: Immediately post the education program.

(3) Post-test 2: 2 months post implementation of the new screening tool.

For cohort 1, paper-based surveys will be collected by those who deliver the education program. For cohort 2, all surveys will be returned to researchers via registered post.

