### Data analysis

*Quantitative data:* Using SPSS, demographic data and responses on all Likert scaled surveys and rating scales, will be analysed descriptively. To see if there is a significant difference between mean scores at Pre-test, Post-test 1 and Post-test 2, where there are three or more mean values to compare together, a one way Analysis of Variance (ANOVA) will be used. Where there are only two mean values to compare, an Independent Samples t-test will be used. Comparisons between groups will be measured according to profession, years of clinical practice, and hospital site. We will determine whether the education intervention resulted in a statistically significant conceptual change to the new form, and whether the education intervention requires further development in terms of content and delivery.

With respect to statistical power and sample size calculations: we are seeking significant differences at the 95% confidence level, so *α* = 0.05. Further, we aim to achieve a statistical power of *π* = 0.8, and to detect effect sizes of Cohen’s *d* = 0.4 and larger. The corresponding sample size required is calculated to be *n* = 50 (using the program *Power and Sample Size v.3.0, 2009*) [25]. Cohort 1 will have the requisite *n* = 50 and Cohort 2 is expected to be at least twice as large as this.

*Qualitative data:* Thematic analysis will be employed to analyse the qualitative data from the semi-structured telephone interviews and the textual responses to open ended questions in the surveys. Themes reflect recurrent and distinctive features of participants’ accounts, characterising particular perceptions and/ or experiences seen as relevant to the research questions [26].

The audio-recorded interviews will be transcribed verbatim in Word and the text transferred into Excel. One researcher will develop initial descriptive codes of the responses to each prompt of the semi-structured interview. A second researcher will check the transcripts, review the initial descriptive codes, and the two researchers will discuss and finalise the framework for analysis. The responses from the focus group participants will be coded using this revised framework and categories identified. Finally, a frequency count for each focussed code will be conducted.

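### At Post-test 2 the effect of the education cannot be separated from the parent trial's replacement of the FRAT, yet primary outcome (i) and aim (iii) credit the change to the education

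*Protocol article*

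**What the plan says.** The protocol article makes the causal claim in three places:

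- **Background, aim (iii):** "Determine the effectiveness of the educational program content and delivery in supporting behaviour change for falls screening in hospitals".
- **Primary outcome measures, item (i):** "Conceptual and behavioural change from utilising the historical FRAT".
- **Data analysis:** "We will determine whether the education intervention resulted in a statistically significant conceptual change to the new form".

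The Design section describes a parent trial that randomises ten hospitals, with "five hospitals using a new Falls Screening Tool" and "five hospitals continuing to use the historical FRAT form". On the form itself it says: "The new Falls Screening Tool removes the risk assessment component from the historical FRAT form and associated summary scores". On the setting it says: "This education trial will be conducted at the 5 intervention hospitals".

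Data collection sets three survey waves: Pre-test just before the session, Post-test 1 just after it, and Post-test 2 "2 months post implementation of the new screening tool". Data analysis compares mean scores across these waves and between subgroups defined by profession, years of practice and site. Strengths and limitations names competing demands on time, recall bias in self-report, and loss to follow-up at the last survey.

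**The concern.** In these five hospitals, moving off the FRAT is the parent trial's own intervention. By Post-test 2 the form has been changed by allocation, whether or not a clinician learned anything from the session, and the respondent has had two months of experience with its replacement. A single-group comparison of waves sees the sum of these influences.

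Behaviour is the sharper problem. Post-test 1 follows the session immediately, so changed screening practice can be reported only at Post-test 2 or in the post-implementation interviews. The behavioural half of a primary outcome is thus observable only after the form has been replaced.

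At stake is the headline conclusion. As written, the plan would report a favourable Pre-test to Post-test 2 difference as an effect of the education when the roll-out may have produced it. It would equally report an unfavourable difference as a failure of the education when dislike of the new form may have cancelled a real benefit. The limitations would not alert the reader to either.

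**Working it through.** **1. Who is exposed to what, and when**

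| Wave | Education received | Two months' use of the new form |
|---|---|---|
| Pre-test | no | no |
| Post-test 1 | yes | no |
| Post-test 2 | yes | yes |

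The rows follow from Design and Data collection. No surveyed group has the new form without the education, or the education without the new form, at the time of Post-test 2. The subgroups in Data analysis (profession, experience, site) all share the same exposure. The interviews come from two of the same hospitals after implementation, so they can describe how the education contributed but cannot isolate its effect.

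**2. What each contrast estimates**

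Let E1 be the immediate effect of the session, E2 the part of it remaining at Post-test 2, and R the effect of the form change plus two months of use. Leave out time trends and interaction, which only add unknowns.

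- Post-test 1 minus Pre-test = E1
- Post-test 2 minus Pre-test = E2 + R
- Post-test 2 minus Post-test 1 = (E2 − E1) + R

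The second and third lines contain two unknowns that always appear as the sum E2 + R. Knowing E1 does not help, because E2 need not equal E1. For illustration, an observed difference of 0.4 standard deviations fits each of these equally well:

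- E2 = 0.4, R = 0 (all education)
- E2 = 0, R = 0.4 (all roll-out)
- E2 = 0.6, R = −0.2 (roll-out masks part of the education effect)

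**3. The plan's sample size**

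Data analysis gives α = 0.05, power 0.8, d = 0.4 and n = 50. A paired, two-sided normal approximation (sidedness is not stated, so two-sided is assumed) gives

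n = ((1.960 + 0.842) / 0.4)² = 49.06, rounded up to 50.

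The figure reproduces as a paired calculation. The present point does not depend on it, and no corrected n exists, because this is a question of identification and not of precision.

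**4. What a significance test at Post-test 2 would do**

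Assume E2 = 0 and let the roll-out alone shift scores by R. The values of R are assumptions; the documents give none. The probability of a significant Pre-test to Post-test 2 difference at two-sided 0.05 is:

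| R (standardised) | Paired, n = 50 | Paired, n = 100 | Independent, 50 per wave | Independent, 100 per wave |
|---|---|---|---|---|
| 0.2 | 0.28 | 0.51 | 0.17 | 0.29 |
| 0.3 | 0.55 | 0.84 | 0.32 | 0.56 |
| 0.4 | 0.79 | 0.98 | 0.51 | 0.80 |
| 0.5 | 0.93 | >0.99 | 0.70 | 0.94 |

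The paired columns standardise by the SD of within-person differences. The independent columns use the SD of scores and correspond to the two-sample t-test that Data analysis names. Size 50 is Cohort 1; size 100 is the lower bound expected for Cohort 2 (twice 50). More respondents raise the chance of a wrong attribution and do nothing to remove it.

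**The case against.** The strongest reply is that the design is openly an uncontrolled before-and-after study inside the intervention arm, that the education is presented as support for implementation, and that a clean contrast, Pre-test to Post-test 1, is already collected. The Data analysis sentence that credits the education speaks of conceptual change, not behaviour. The behaviour the program targets is also wider than dropping a form: it includes clinical reasoning in choosing interventions, which a new form does not produce by itself. All of this is fair, and it is why the remedy is one of labelling and not of redesign. It does not remove the problem, because the primary outcome names no wave, aim (iii) still speaks of effectiveness for behaviour change, and that behaviour can be reported only after the roll-out.

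A reader might go further and infer that a positive result at Post-test 2 is practically guaranteed. The documents do not support that. The Instruments section describes choices among statements of view, agreement items, perceived benefit, relevance items and free text, and no count of FRAT use. Two months with a new form could worsen such answers; the risk section itself foresees anxiety about new recording methods. Nor do the documents give a rate of FRAT use after the switch. That it would be low is an inference from allocation and assumes adherence.

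Surveying control-hospital staff might seem the obvious cure. It would help with time trends, but under the stated allocation those staff keep the FRAT and are outside the education study, so the contrast would still estimate education and roll-out together.

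**Conclusion.** The point holds, limited to Post-test 2. Education and form replacement are fully aliased there, in either direction, and the education share of any change is unidentified. This follows from the allocation, the timing and the absence of a comparator, and not from any assumed figure; the probabilities in the table are illustrations only. Stopping FRAT use is the clearest case, since it is expected from allocation alone if hospitals adhere.

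It would be too strong to say that aim (iii) as a whole cannot be answered. Views on content and delivery are also gathered through the relevance items, the learning-experience items, the open questions and the interviews. Pre-test to Post-test 1 can show an immediate change in views and knowledge. That contrast is uncontrolled too, but it closely brackets the session and leaves no interval for two months of using the form.

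**What to change.** - **Primary outcome measures and Data analysis:** split item (i). Name the Pre-test to Post-test 1 change in views and knowledge as the education contrast, and state that it is uncontrolled.
- **All Post-test 2 results:** report them as the combined effect of education plus roll-out. This includes any behaviour, practice and confidence items, which are aliased in the same way and cannot stand in as a cleaner measure of behaviour.
- **Stopping FRAT use:** do not use it as evidence that the education was effective.
- **Aim (iii):** limit only the behaviour-change part to the combined effect. The part on content and delivery can stay.
- **Strengths and limitations:** add the missing comparator and the replacement of the form by the parent trial.

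No data collection changes. The cost is wording and a narrower claim at Post-test 2.

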#### Secondary outcome

Participants’ evaluations of the education program to inform the future refinement of educational delivery to clinicians.

### Data analysis

*Quantitative data:* Using SPSS, demographic data and responses on all Likert scaled surveys and rating scales, will be analysed descriptively. To see if there is a significant difference between mean scores at Pre-test, Post-test 1 and Post-test 2, where there are three or more mean values to compare together, a one way Analysis of Variance (ANOVA) will be used. Where there are only two mean values to compare, an Independent Samples t-test will be used. Comparisons between groups will be measured according to profession, years of clinical practice, and hospital site. We will determine whether the education intervention resulted in a statistically significant conceptual change to the new form, and whether the education intervention requires further development in terms of content and delivery.

With respect to statistical power and sample size calculations: we are seeking significant differences at the 95% confidence level, so *α* = 0.05. Further, we aim to achieve a statistical power of *π* = 0.8, and to detect effect sizes of Cohen’s *d* = 0.4 and larger. The corresponding sample size required is calculated to be *n* = 50 (using the program *Power and Sample Size v.3.0, 2009*) [25]. Cohort 1 will have the requisite *n* = 50 and Cohort 2 is expected to be at least twice as large as this.

*Qualitative data:* Thematic analysis will be employed to analyse the qualitative data from the semi-structured telephone interviews and the textual responses to open ended questions in the surveys. Themes reflect recurrent and distinctive features of participants’ accounts, characterising particular perceptions and/ or experiences seen as relevant to the research questions [26].

The audio-recorded interviews will be transcribed verbatim in Word and the text transferred into Excel. One researcher will develop initial descriptive codes of the responses to each prompt of the semi-structured interview. A second researcher will check the transcripts, review the initial descriptive codes, and the two researchers will discuss and finalise the framework for analysis. The responses from the focus group participants will be coded using this revised framework and categories identified. Finally, a frequency count for each focussed code will be conducted.

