### Strengths and limitations

This study is unique and the educational program can be delivered in a busy, time pressured clinical environment using clinical champions (leaders) and a ‘train the trainer’ approach. We shall clearly report the educational features so that others can adopt a best practice approach to educational design. The education interventions are designed to be readily implemented across other hospital sites and applied to other clinical education interventions. This study is not without limitations. There is a time factor related to educating Cohort 2, and education on a new clinical form may not be seen as a high priority for clinicians in a busy clinical environment with competing demands on time. There is also the potential for inaccurate self-reporting caused by recall bias [30] influenced by different clinicians’ perceptions. Loss to follow up is also likely, particularly for post survey 2 when moving from paper based surveys to online surveys.

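### Pre-test, Post-test 1 and Post-test 2 come from the same clinicians, but the plan compares them with tests for independent groups

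*Protocol article*

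**What the plan says.** The Data analysis section of the protocol article asks whether mean scores differ between the three survey waves. Its rule is: "where there are three or more mean values to compare together, a one way Analysis of Variance (ANOVA) will be used". It continues: "Where there are only two mean values to compare, an Independent Samples t-test will be used". Comparisons by profession, years of practice and hospital site follow in a separate sentence. No paired test, repeated-measures ANOVA or mixed model appears anywhere in the article.

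The design is within-person. Under Participants and recruitment methods, attendees in each cohort complete the Pre-test and Post-test 1 on the day of their education, with Post-test 2 to follow online. Under Data collection, surveys are identified by the participant's "initials and last three digits of their mobile telephone number". Under Instruments, 13 items are carried over from the Pre-test.

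The sample size paragraph in Data analysis states: "we are seeking significant differences at the 95% confidence level"; "we aim to achieve a statistical power of *π* = 0.8"; "to detect effect sizes of Cohen’s *d* = 0.4 and larger"; and "The corresponding sample size required is calculated to be *n* = 50". Cohort 1 is to have 50 participants and Cohort 2 at least twice that.

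Strengths and limitations adds: "Loss to follow up is also likely, particularly for post survey 2 when moving from paper based surveys to online surveys".

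**The concern.** An independent-samples t-test and an ordinary one-way ANOVA both take the variance of a difference between waves to be the sum of two unrelated variances. When one person supplies both scores, the covariance between them has to be subtracted. Leaving it out gives the wrong standard error, confidence interval and p-value.

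Two of the three primary outcomes are changes (conceptual and behavioural change, and change in knowledge), so the main answer is affected. The plan will also use these tests to decide whether the education produced a significant conceptual change and whether it needs further development. A falsely null result would mislead that decision.

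There is a second consequence. Unlinked wave means compare everyone who answered the Pre-test with only those who answered Post-test 2, where the article itself expects loss. Part of any difference can then reflect who replied.

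**Working it through.** **Inputs from the protocol article (Data analysis):** alpha 0.05 (sidedness not stated; two-sided taken), power 0.80, d = 0.4, n = 50 in Cohort 1, at least 100 in Cohort 2. **Assumption:** the within-person correlation ρ is not given, so 0.3, 0.5 and 0.7 are shown.

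**1. Reproducing n = 50**

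- Paired, two-sided: n = ((1.960 + 0.842)/0.4)² = 49.06, rounded up to 50. The exact paired t calculation gives 51.01, so 52.
- Independent samples, two-sided: n per time point = 2 × 49.06 = 98.1, so 99. The exact t calculation gives 99.08, so 100.
- One-sided versions give 39 (paired) and 78 per time point (independent).

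The stated figure fits only a two-sided paired calculation, with d standardised by the SD of the within-person change. It does not fit the t-test that the plan names.

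**2. Standard error**

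With a common score SD σ, the true variance of the mean change is 2σ²(1 − ρ)/n, while the independent test uses 2σ²/n. Its standard error is therefore too large by a factor of 1/√(1 − ρ).

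**3. Two waves, n = 50, shift of 0.4 score SD**

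The effect in change-SD units is 0.4/√(2(1 − ρ)), which equals 0.4 at ρ = 0.5. The critical value of the independent test is 1.984 on 98 degrees of freedom, so its true type I error is approximately 2(1 − Φ(1.984/√(1 − ρ))).

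| ρ | SE too large by | Type I error, independent | Power, independent | Power, paired |
|---|---|---|---|---|
| 0.3 | 1.20 | 1.8% | 51% | 65% |
| 0.5 | 1.41 | 0.5% | 51% | 79% |
| 0.7 | 1.83 | 0.03% | 51% | 95% |

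Simulation with 10,000 runs agrees: type I error of the independent test was 2.1%, 0.6% and 0.05%, while the paired test stayed near 5%.

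**4. Three waves, n = 50** (simulation, 10,000 runs, equal correlations, shift of 0.4 SD at both post-tests)

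| ρ | Power, one-way ANOVA | Power, repeated-measures ANOVA | Type I error, one-way ANOVA |
|---|---|---|---|
| 0.3 | 48% | 67% | 1.5% |
| 0.5 | 47% | 84% | 0.3% |
| 0.7 | 44% | 97% | below 0.1% |

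**5. Cohort 2, n = 100, two waves**

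The independent t-test has 85%, 89% and 94% power at ρ = 0.3, 0.5 and 0.7, against 92%, 98% and 99.9% for the paired test.

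**6. Who replies to Post-test 2 (illustration only)**

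Suppose 60% reply, and at Pre-test the repliers stood 0.3 SD above the non-repliers. With no change in anyone, the unlinked comparison shows (1 − 0.6) × 0.3 = +0.12 SD. Neither the 60% nor the 0.3 SD is in the article.

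**The case against.** **The text may be a wording fault.** The t-test sentence names no time points and stands just before the group comparisons, where an independent test is the right type. One-way ANOVA can also have a repeated-measures form, and n = 50 suggests that the planners had paired data in mind. This is possible. But the ANOVA sentence is expressly about the three survey waves, the t-test sentence continues the same rule for two means, and nothing paired is named. Followed as written, the plan gives the wrong analysis, and its sample size contradicts it.

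**The error is conservative.** This stands. With positive within-person correlation, ignoring the pairing does not produce false positives. The cost is lost power and intervals that are too wide.

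**Cohort 2 is large enough.** This stands in part. At 100 participants the independent t-test exceeds 80% power for a 0.4 SD shift. Its p-values and intervals remain wrong, and Cohort 1 is left at about even odds.

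**The selection point rests on invented inputs, and a paired test uses only completers.** The 0.12 SD is indeed only an illustration. A paired test stops the comparison of different sets of people, but it does not make repliers represent non-repliers. A mixed model helps there only if the missing surveys are missing at random.

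**Linkage is inferred.** The article presents the code as a means of de-identification and does not say that it will be used for matching. It nevertheless makes matching possible.

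**Conclusion.** The point holds and must be fixed. The plan names independent-groups tests for repeated measurements on the same people, and its sample size of 50 fits only a paired test. That contradiction depends on no assumed correlation.

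For Cohort 1, with a shift of 0.4 score SD, power is about 51% as written, against 65% to 95% with pairing for ρ from 0.3 to 0.7. True type I error falls to between 1.8% and 0.03%. For three waves, one-way ANOVA has 44% to 48% power against 67% to 97%. These figures assume full response and, for three waves, equal correlations. At ρ = 0 nothing would be lost, but that is implausible for one person answering the same items twice on one day. In Cohort 2 the loss of power is modest, though the error term is still wrong.

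**What to change.** Reword the across-time sentences in Data analysis:

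- Link each person's surveys by the personal code.
- Within each cohort, fit a linear mixed model for repeated measures to all available surveys. Use time as a three-level fixed factor, a participant random effect or an unstructured covariance, and hospital as an added effect. State the missing-at-random assumption.
- Report Pre-test to Post-test 1 and Pre-test to Post-test 2 as within-person contrasts with 95% confidence intervals. A paired t-test is the simple fallback for two waves.
- Restrict these contrasts to items worded identically at the waves compared. Six items change at Post-test 1, and three undergo minor changes at Post-test 2.
- Keep the independent t-test and one-way ANOVA for comparisons between different people (profession, years of practice, site).
- State that n = 50 is for a paired test and which SD standardises d = 0.4. If it is the score SD, the paired requirement depends on the correlation: 71, 52 or 32 people at ρ = 0.3, 0.5 or 0.7.

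The cost is mainly wording. The code is already collected and SPSS, already in use, fits mixed models. The plan must also say how unmatched or duplicate codes are handled, and the analysis is limited to the unchanged items.

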**Discussion:**

This study will quantify the outcomes of a high-quality clinician education program to increase knowledge of evidence-based practice for falls prevention. It is predicted that positive behavioural changes will occur in health professionals, leading to organisational change and improved patient outcomes. Furthermore, the findings from the study will inform the future refinement of educational delivery to health professionals across hospital sites.

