### Participants and recruitment methods

At each of the intervention hospitals, there will be two separate cohorts. The names and contact details of all potential participants will be obtained from an existing hospital database.

*Cohort 1*: (*n* = 10 clinical leaders at each experimental hospital), will be approached by the Hospital General Manager to consider participating in the study. These clinical leaders will be invited to participate via email, which will contain all details about the study, the requirements for participation, and the Participant Information and Consent Form (PICF) (Additional file 1). On the day of the education, cohort 1 will be required to complete the written PICF, Pre-test and Post-test 1 surveys and return them to the researcher who is leading the education program. The PICF will also include consent to participate in a follow up telephone interview. Only those providing their contact details and consent will be contacted to participate in the interviews. Completing the Post-test 2 survey online will imply consent.

*Cohort 2:* (*n =* All nurses and allied health professionals involved in completing falls screening), will be eligible to participate and will be invited to attend a one-hour in-service education program. Staff will be asked to read the PICF (Additional file 2), which outlines the full details of the research project and the requirements for participation. Participants will be drawn from all wards in the five intervention hospitals, excluding paediatric, maternity, emergency and theatre wards. We are aiming for 65% attendance of all nurses and allied health professionals at each experimental site. On the day of the in-service training, cohort 2 will be required to complete the written PICF, Pre-test and Post-test 1 surveys. These will then be returned to the researchers via registered post. The PICF will also include consent to participate in a follow up telephone interview. Only those providing their contact details and consent will be contacted to participate in the interviews. Completing the Post-test 2 survey online will imply consent.

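### The single power claim (n = 50, 80%, d = 0.4) fits only a paired whole-cohort change, yet it is left unrestricted beside planned comparisons by site, profession and experience

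*Protocol article*

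**What the plan says.** Under Data analysis, the protocol article names a one-way ANOVA where three or more means are compared and an independent-samples t-test where there are two. It then adds: "Comparisons between groups will be measured according to profession, years of clinical practice, and hospital site". These comparisons are not labelled exploratory, and no group sizes are given for profession or experience.

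The next paragraph holds the only power statement: "we are seeking significant differences at the 95% confidence level, so *α* = 0.05"; "we aim to achieve a statistical power of *π* = 0.8"; "to detect effect sizes of Cohen’s *d* = 0.4 and larger". It continues: "The corresponding sample size required is calculated to be *n* = 50". It then says "Cohort 1 will have the requisite" number, and that Cohort 2 should be at least twice that size. No contrast is named for d = 0.4.

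Under Participants and recruitment methods, Cohort 1 is 10 "clinical leaders at each experimental hospital". The Design section gives five intervention hospitals, so 50 is the whole of Cohort 1. Cohort 2 has no fixed number, only a target of 65% attendance.

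**The concern.** A reader meets the group comparisons and, directly afterwards, an unqualified statement that the study can detect d = 0.4 or more with 80% power. Nothing says that this covers one kind of contrast and not the other. If 50 is all of Cohort 1, any comparison between parts of Cohort 1 rests on far fewer people per group.

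A non-significant difference between sites would then be the expected result even if two sites truly differed by 0.4 SD. Set beside the stated 80%, it could be mistaken for evidence that the program works equally well everywhere.

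There is a second, smaller problem. Neither named test carries a baseline term. If post-test means are compared by group, a site or profession that started higher cannot be told apart from one that learned more, although Pre-test answers are collected and a participant code allows linkage.

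**Working it through.** **Inputs.** From Data analysis: alpha 0.05, power 0.80, d = 0.4, n = 50, and Cohort 2 of at least 100. From Participants and recruitment methods and Design: 10 leaders at each of 5 hospitals. Assumed, because not stated: two-sided tests, full response, no multiplicity correction, 0.4 SD as the largest gap between groups, 20 per site in Cohort 2 at its floor, and the splits by profession or experience.

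**1. The plan's own figure.** Paired (one-sample) formula:

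n = ((1.960 + 0.842) / 0.4)² = 49.06, rounded up to 50.

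The exact paired t-test needs 51.0, and its power at n = 50 is 79.2%. Here d is the mean change divided by the SD of the changes; this equals the usual between-person d only if the two waves correlate at 0.5.

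Other readings do not give 50:
- independent two-sample, two-sided: 99 per group
- independent two-sample, one-sided: 78 per group
- paired, one-sided: 39–40

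So 50 is a paired, whole-cohort number.

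**2. The same contrast with the named test.** If the two waves are treated as independent groups of 50, the noncentrality is 0.4 × √(50 × 50 / 100) = 2.0 on 98 df, and power is 51%.

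**3. Two-group comparisons within Cohort 1.** Noncentrality = 0.4 × √(n₁n₂ / (n₁ + n₂)), noncentral t:

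| Split | Noncentrality | Power at d = 0.4 | d detectable with 80% power |
|---|---|---|---|
| 10 v 10 (two sites) | 0.89 | 13.5% | 1.32 |
| 10 v 40 (one site v the rest) | 1.13 | 19.8% | 1.01 |
| 15 v 35 | 1.30 | 24.6% | 0.88 |
| 25 v 25 (best two-way split) | 1.41 | 28.3% | 0.81 |

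**4. Five-site one-way ANOVA.** f² is the mean squared deviation of the site means in SD units; noncentrality = N × f²:

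| Site means (SD units) | f² | Power, N = 50 | Power, N = 100 |
|---|---|---|---|
| 0, 0.2, 0.2, 0.2, 0.4 | 0.0160 | 8.9% | 13.9% |
| 0, 0.1, 0.2, 0.3, 0.4 | 0.0200 | 10.0% | 16.5% |
| 0, 0, 0, 0, 0.4 | 0.0256 | 11.5% | 20.3% |
| 0, 0, 0.4, 0.4, 0.4 | 0.0384 | 15.3% | 29.4% |

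N = 100 is Cohort 2 at its floor. There, two sites of 20 have 23% power and a 50 v 50 split has 51%.

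**5. What Pre-test adjustment buys.** Approximating ANCOVA by d / √(1 − ρ²), with an assumed ρ of 0.5 to 0.7, the effective d is 0.46 to 0.56. Cohort 1 power becomes 16–22% (10 v 10) and 36–49% (25 v 25). Adjustment removes baseline differences but does not bring these comparisons near 80%.

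**6. Where a Pre-test value exists.** Under Instruments, 13 of the 20 evidence-based-practice items return unchanged at Post-test 1, 6 are reworded, 1 is dropped and 4 are new. The IMMS relevance items and the five learning-experience items first appear at Post-test 1, so they have no baseline.

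**The case against.** The strongest reply is that nothing has been miscalculated. The figure of 50 reproduces, it is matched to Cohort 1 as a whole, and the first two primary outcomes are changes, not contrasts between sites or professions. Powering the main change and also reporting subgroup comparisons is ordinary practice. This stands: the protocol never expressly promises 80% power for the group comparisons.

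A reader might also infer that the site comparisons decide whether content and delivery are revised, and that a non-significant result will be read as uniform effect. The text supports neither. The secondary outcome ties refinement to participants' evaluations. The abstract's statement that "the findings from the study will inform the future refinement of educational delivery to health professionals across hospital sites" is about the study's findings as a whole and describes no site contrast. No section says how a non-significant difference will be interpreted.

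The low figures are for the smaller cohort. Cohort 2 takes in all eligible staff at five hospitals, and 100 is only a minimum; with about 99 per group, d = 0.4 would be detectable. That also stands.

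On baseline, the sentence does not say which scores are compared. Comparing Pre-test views between groups would serve the first aim and needs no adjustment, and the program ratings cannot be adjusted at all. Adjustment therefore applies only to items repeated unchanged, when groups are compared on their response to the education.

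What the reply does not remove is that one unrestricted claim sits beside two kinds of contrast and fits only one of them. That is a fault in the claim as written, not a detail left to an analysis plan.

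**Conclusion.** The point holds as an error of scope in the power claim. The stated 80% is about right (79%) only for a whole-cohort pre-post change analysed as paired data with all 50 responding. The independent t-test that the section names would give about 51% for that same contrast. The article itself expects loss to follow-up, mainly at Post-test 2, so 79% is a ceiling for Cohort 1 at that wave.

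For the Cohort 1 group comparisons, power at d = 0.4 is about 9–28%. This range rests on the assumptions listed in the working; dropout or multiplicity correction would lower it. Cohort 2 at its floor does little better across sites (14–29%), but its final size is open and no conclusion can be drawn for a larger cohort.

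It would go too far to say that the sample size is wrong, or that the protocol claims 80% power for subgroups. The baseline point is narrower still: it concerns comparisons of response to the education on items that have an identical Pre-test version.

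**What to change.** In the Data analysis section:

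1. State that n = 50 and about 80% power apply only to the whole-cohort pre-post change, analysed as paired data with full response. The named test for that contrast has to change to match. State that the Cohort 1 comparisons by site, profession and experience are exploratory, and give the differences detectable with 80% power: about d = 1.3 for two sites (10 v 10) and about 0.8 for an even two-way split (25 v 25).
2. Report group differences as estimates with 95% confidence intervals, and say that a non-significant difference will not be taken as evidence of equal effect.
3. For items worded identically at Pre-test, compare groups on response to the education using the same person's Pre-test score, by ANCOVA or a group-by-time term in a mixed model. Three items are reworded at Post-test 2, so check which still match at that wave. The IMMS, learning-experience and new items stay unadjusted.

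The cost is a few sentences, slightly more analysis work and a less favourable stated power for the group comparisons. No further participants or data are needed.
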